**Fig. 1 Fig1:**
[figure not shown]
Study flowchart. Flowchart of planned participants’ selection and study design

The study is designed to detect a moderate effect size (d = 0.60, f = 0.35), as observed in the meta-analysis for CT for SAD with intense BE and prolonged sessions, as compared to CT with a reduced number of BEs and shortened sessions [7]. A power analysis with 90% power on a two-sided test where α = 0.05 revealed a sample size of *N* = 54 (27 per group). Based on data from previous studies [5], we expect a drop-out rate of 10%. Thus, 60 patients (30 per group) will have to be recruited.

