## Background

Social anxiety disorder (SAD) is a highly prevalent and chronic psychiatric disorder associated with considerable psychosocial impairment. In recent years, growing evidence has suggested that individual cognitive therapy (CT) based upon the Clark and Wells model [1] may be superior to some alternative cognitive behavioral therapy (CBT) approaches, as well as to other treatment modalities. Six randomized controlled trials in three different countries have compared individual CT with alternative active treatments; individual CT was proven to be significantly more effective. Individual CT outperformed two versions of group CBT [2, 3], in vivo exposure [4], interpersonal psychotherapy [5], psychodynamic short-term psychotherapy [6], fluoxetine plus self-exposure instructions [4], and medication-based treatment as usual [3]. Mayo-Wilson et al. [7] reported a network meta-analysis of 101 randomized controlled trials on 41 psychological and pharmacological treatments and again demonstrated the highest effect sizes for Clark & Wells’ individual CT and a related individual CBT developed by Heimberg and colleagues.

Although the finding that individual CT is superior to other comparable treatments is consistent across studies in three European countries, Mayo-Wilson et al. [7] found that there was a significant difference in the magnitude of within CT change between English trials [4] [8] and German [2, 5, 6] and Swedish [3] trials. The standard mean difference compared to no treatment was − 1.56 for the English trials and − 0.97 for the German and Swedish trials.

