There are several possible factors that may account for the differences between the two sets of trials. First, when comparing trials against the Clark et al. ones, the allegiance to the treatment may differ between researchers and therapists. Although the influence of researcher allegiance was minimized by the inclusion of D.M. Clark in the training, implementation and publication of the data of all trials, there are no data that allow for a direct comparison of therapist allegiance. Second, in the English trials almost all sessions were 90 min long to arrange the implementation of out of office behavioral experiments; however, in the German and Swedish trials, most therapists used shorter sessions lasting 50 min, which is in line with healthcare standards, but provides insufficient time to effectively set-up and discuss the results of in-session behavioral experiments. Evidence in support of this concern comes from a recent analysis [9] of video tapes and therapist protocols of CT treatments from the SOPHONET trial, a large-scale multicenter randomized controlled trial [6] comparing the efficacy of CT and short-term psychodynamic psychotherapy in Germany. Therapists protocols from *N* = 165 completed treatments disclosed which treatment interventions were actually applied in the sessions. Results indicated that almost all therapists applied basic cognitive interventions, such as deriving a cognitive model, roleplaying to avoid safety behaviors and self-attention, video feedback, and verbal techniques of cognitive restructuring (e.g., Socratic dialogue). In contrast, the frequency of behavioral experiments (BE) was significantly reduced compared to the required standard in the manual (the mean frequency in treatment was 1.7, versus a mean recommended frequency of 6). Furthermore, the analysis of the duration of the sessions revealed that the vast majority of sessions (on average 17 out of 25) lasted only 50 min. This indicates that the preference for 50-min sessions, as is usual in healthcare for psychotherapy settings, may have been one of the reasons for the low rate of BEs in the study.

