Standard CT comprises similar elements in the first and third stage of therapy; however, in the middle stage (stage 2), discussion techniques of challenging dysfunctional beliefs are used instead of BE. The techniques are described in detail in the previous manual [17] and include Socratic dialogue, the downward arrow technique, the prejudice technique, the life chart technique, positive data log, automatic thoughts protocol, and the pie chart technique. Dysfunctional beliefs associated with early experiences are identified and discussed. Homework mainly focuses on automatic thoughts and the practice of Socratic dialogue.

In standard CT, therapists are not encouraged to use BEs. Neither exposure based on a habituation rational nor formal social skills training is used.

To equalize therapists’ contact time and treatment dose, both treatments comprise the same amount of contact hours. In line with short-time-therapy in Germany, 25 units of 50-min duration are provided. In CT + BEs, up to eight sessions last 100 min due to the implementation of BEs. Standard CT includes one session of 100-min duration. Thus, the total number of sessions differs (17 vs. 25). The length of both treatments, however, is 6 months, since booster sessions are conducted (4-week interval) in the end of CT + BEs as prescribed in the manual.

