In the current study, the two active treatment conditions differ with respect to one component: BE. Thus, this study may be categorized as a dismantling study [42, 43], decomposing a multi component therapy by removing one component expected to be an effective ingredient. The expected effect size for the difference between a treatment including or not including one component usually is expected to be small, requiring large sample sizes to detect significant differences. For instance, a meta-analysis by Bell et al. [43] confirmed that the effects in dismantling studies were very small and nonsignificant. Thus, a high number of participants is needed to detect significant differences. However, Bell et al. also found that additive studies show significant, although small, effects of additive components. Thus, it is of importance whether an effective treatment package is decomposed, or an effective treatment component is added. The present study may rather be classified as an additive study, because a new component (BEs aiming at new emotional experiences) is added to traditional CT (using mainly verbal methods to achieve insight). In our study, BEs are a vital part in the therapy. Therapists are encouraged to implement BEs over a large number of sessions, so the differences between both groups might be greater than in conventional dismantling studies.

Another potential limitation that may impair the validity of the previous studies comparing BEs to exposure is the allegiance of researcher and therapists. Much of the effects of psychological treatments may be attributed to the effect of allegiance [44]. Therefore, we attempt to control for possible biases due to an imbalance between both conditions by several measures: Firstly, we randomize therapists to one of both conditions and train them separately. Secondly, although missing behavioral experiments, we prevent a possible devaluation of the control condition by emphasizing the particular benefit of cognitive restructuring for strengthening self-esteem. Thirdly, we will check for possible differences in allegiance between both conditions using the therapist version of the Reaction to Treatment Questionnaire developed by Holt & Heimberg [32].

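### The planning effect d = 0.60 is presented as an observed effect of behavioral experiments, but it matches an indirect difference between trial sets, and 27 per group does not give 90% power for it

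*Protocol article*

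**What the plan says.** All places are in the protocol article.

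- **Design and Sample Size:** the planning effect is d = 0.60, also written as f = 0.35 and called moderate. Its origin is described in these words: "as observed in the meta-analysis for CT for SAD with intense BE and prolonged sessions, as compared to CT with a reduced number of BEs". The low-BE therapy is said to have had shorter sessions too, and one network meta-analysis is cited. At 90% power and two-sided α = 0.05 this is said to give N = 54 (27 per group), raised to 60 for 10% drop-out.
- **Background, on the same meta-analysis:** "The standard mean difference compared to no treatment was − 1.56 for the English trials and − 0.97 for the German and Swedish trials". The section then turns to explanations of this gap: "There are several possible factors that may account for the differences between the two sets of trials". It discusses allegiance, session length, the number of behavioral experiments (BEs), and therapist competence with training and supervision. It also says there is as yet no direct evidence that systematic use of BEs affects the outcome of cognitive therapy (CT).
- **Treatments, on standard CT:** "in the middle stage (stage 2), discussion techniques of challenging dysfunctional beliefs are used instead of BE". On dose: "To equalize therapists’ contact time and treatment dose, both treatments comprise the same amount of contact hours".
- **Discussion:** the effect of a single component is usually expected to be small, and "additive studies show significant, although small, effects of additive components". The authors class their trial as additive and argue that the difference here might be larger than in conventional dismantling studies.

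**The concern.** A reader of the sample-size paragraph will take 0.60 as an evidence-based estimate of what BEs add over this control, backed by 90% power. Neither part is supported. The effect appears to be a gap between two groups of trials run in different countries, each measured against no treatment. The comparator in the sizing statement has few BEs, whereas the control arm has BEs replaced. The article's own evidence on added components points to small effects, and the Discussion does not derive 0.60 in reply.

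What is at stake is how the result of Hypothesis 1 can be understood. If the true effect is well below 0.60, a non-significant result is likely even if BEs help, and the stated planning figures would hide this.

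**Working it through.** **1. Source of the effect.** Inputs from the Background: SMD −1.56 (English trials) and −0.97 (German and Swedish trials), both against no treatment.

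1.56 − 0.97 = 0.59, which rounds to 0.60.

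The sample-size paragraph does not show this subtraction. The link is inferred from the shared reference and the matching arithmetic.

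**2. Source contrast and trial contrast, side by side.**

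| Factor | Between the two trial sets (Background) | Between the arms of this trial |
|---|---|---|
| Therapist pool | different countries and trials | one training center, therapists randomized |
| Total contact time | not reported; session length differed | equal, 25 units of 50 min |
| Amount of training and supervision | may have been insufficient in the German trials | three 8-h days and continuous supervision in both arms |
| Training content, supervisor | not separated | differ by arm |
| Session length | mostly 90 min vs mostly 50 min | up to eight vs one session of 100 min |
| BE dose | low set: mean 1.7 against 6 recommended (one German trial) | BEs central vs replaced by verbal techniques |
| Allegiance | may differ, no direct data | measures to balance it, yet Hypothesis 2 predicts it to be higher with BEs |

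The first three rows would tend to narrow the contrast. The others retain it or could widen it. The documents do not allow a net direction to be derived.

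**3. The stated sample size.** Inputs: d = 0.60, two-sided α = 0.05, 90% power, 1:1 allocation.

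n per group = 2(1.960 + 1.282)² / 0.60² = 2 × 10.51 / 0.36 = 58.4, so 59 (60 with the t distribution). The total is 118 to 120, not 54.

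The drop-out step does reproduce: 54 / 0.9 = 60.

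**4. What 27 per group delivers.** The noncentrality is d√(n/2) = 0.60 × √13.5 = 2.20. The normal approximation gives Φ(2.20 − 1.96) ≈ 0.60. The noncentral t gives 0.581.

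| True d | Power, 27 per group | Power, 30 per group |
|---|---|---|
| 0.20 | 11% | 12% |
| 0.30 | 19% | 21% |
| 0.40 | 30% | 33% |
| 0.60 | 58% | 63% |

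Detectable d at 27 per group: 0.78 for 80% power and 0.90 for 90% power. The article gives no number for a small effect, so 0.20 to 0.30 is an assumption.

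**5. Could another reading give 54?** For two equal groups f = d/2, so f = 0.35 means d = 0.70. That gives 71% power at 27 per group. N = 54 appears only under assumptions the article does not state. Examples are a repeated-measures between-group test with f = 0.35, three measurements and correlation 0.4, or baseline adjustment with a correlation of about 0.74, from √(1 − 27/59), at d = 0.60.

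**The case against.** The strongest reply is that the article is open about most of this. It reports both SMDs as against no treatment, lists rival explanations, admits the lack of direct evidence, raises the small-effect literature itself, and gives a reason to expect more here: BEs are central and run over many sessions. The control, mostly verbal CT in mostly 50-min sessions, also resembles the low-BE German treatment in the Background. All of that stands as disclosure. It does not turn 0.60 into an observed effect of this comparison, because the Discussion argues only that the difference might be greater.

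Two stronger readings are tempting, and the documents do not support them.

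- **The design equalizes everything behind the 0.59, so the true contrast must be smaller.** Session length is deliberately not equal, double sessions being an obligatory part of the BE arm. Training content and supervisors differ by arm, and Hypothesis 2 expects higher allegiance with BEs.
- **Removing BEs from the control enlarges the effect in proportion to BE dose.** That assumes no BEs at all in the control and a linear dose effect. The article says only that therapists are not encouraged to use BEs, and it gives no dose-response figure.

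It is also fair to say that the 58% comes from the sample-size arithmetic, not from the source of the effect. The two faults are distinct: recalculating N for d = 0.60 would not make 0.60 an estimate for this contrast. Both lie in the same statement, however, and can be corrected together.

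**Conclusion.** The concern holds in a limited form. The documents give no effect estimate for CT plus enhanced BEs against this control. The 0.60 is best read as an indirect difference between trial sets (0.59), confounded by factors that the trial partly balances and partly keeps. Whether it is too large or too small for this trial cannot be settled from the text. The article's own account of added components is a reason for caution about 0.60, not proof that it is too large.

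The 90% power is wrong as stated: about 58% at d = 0.60 with 27 per group, and about 11% to 19% if the effect is in the assumed small range. These figures rest on an unadjusted two-sided t-test of two means, the plainest reading of the sample-size paragraph. They are not the power of the responder comparison that is the primary analysis, for which the article gives no response rates.

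A reader might infer that the authors would take a null result as showing that BEs add nothing. The article does not say so. How a null result will be reported may be covered in an analysis plan that is not shown.

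**What to change.** Keep N = 60 and revise the sample-size paragraph in three places.

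1. Describe d = 0.60 as an indirect difference between two sets of trials (1.56 − 0.97, each against no treatment), used as a planning assumption. Say that it also reflects factors other than BEs, some of which this design holds equal and some of which it does not.
2. Replace the 90% power statement with what the fixed N delivers. For a two-sided t-test at 0.05 with 27 per group, power is about 58% at d = 0.60, and the detectable d is about 0.78 at 80% and 0.90 at 90%. Add about 11% to 19% at d = 0.20 to 0.30, with that range labeled as an assumption. If the original figure came from a repeated-measures or baseline-adjusted calculation, state that model and its correlation.
3. Reconcile the comparator in the sizing statement (few BEs) with the control in the Treatments section (BEs replaced by verbal techniques).

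The cost is a rewording, with no extra patients, visits or data. The downside is a less favorable stated power.

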### Statistical Analyses

Data will be analyzed with the SPSS statistical software package. All statistical analyses will be conducted on the intent-to-treat (ITT) sample and completer sample. Patients allocated to treatments will be classified as drop-outs if they miss more than 25% of the sessions. In the ITT analyses of treatment response, drop-outs will be considered as failures. In ITT analyses of dimensional measures, missing data will be replaced using the last observation carried forward approach for missing intervention- and post-assessments or follow-up observations. Analyses of the primary outcome measure (CGI-I), a categorical variable, will be conducted using χ^2^ or Fisher's exact tests. Dimensional measures will be submitted to analyses of covariance (ANCOVAs) in which pre-treatment scores will be controlled for. ANCOVAS will be performed separately for the post-treatment and 6-month follow-up assessments. Significance levels will be set at *p* < 0.05, two-tailed. Predictor analysis will be calculated by using logistic regression analysis with CGI-I as the dependent variable; independent variables are competencies, adherence, allegiance, and therapist-rated therapeutic relationships (therapist predictors), as well as patients’ preferred learning style at pre-treatment, changes in insight in SAD-related beliefs and cognitions, and patient-rated therapeutic relationships (patient predictors). Differences between treatments in the outcome predictions will be analyzed, with treatment interactions for each predictor. To test for possible therapist differences, a preliminary analysis of covariance will be conducted. As recommended, significance level in this case will be set at *p* < .30 [37]. If the effect is significant, a multilevel analysis using a mixed-model design is planned to include therapists as a random term [38]. A final analysis will be run to compare the pattern of results from both strategies of analysis taking possible therapist effects into consideration.

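### The stated 90% power does not follow from the stated inputs, and the calculation is not for the planned primary test

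*Protocol article*

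**What the plan says.** Methods/Design, Design and Sample Size: "The study is designed to detect a moderate effect size (d = 0.60, f = 0.35"), with the effect attributed to a meta-analysis of CT for SAD. It continues: "A power analysis with 90% power on a two-sided test where" alpha is 0.05 "revealed a sample size of *N* = 54 (27 per group"). A 10% drop-out allowance raises this to 60. The section names no test, endpoint, responder rates or pre-post correlation.

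The Background shows where the effect probably comes from. "The standard mean difference compared to no treatment was" -1.56 in the English trials and -0.97 in the German and Swedish ones, a gap of 0.59 on a continuous scale.

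Outcome Measures and Analysis of Outcome Variables make the primary outcome the proportion of CGI-I responders (rating 1 or 2) at post-treatment. Statistical Analyses says: "Analyses of the primary outcome measure (CGI-I), a categorical variable, will be conducted using" chi-square or Fisher's exact tests. It counts drop-outs as failures in the ITT analysis of response and reserves ANCOVA for dimensional measures. The Abstract, by contrast, names the LSAS as primary.

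**The concern.** A reader can test the sample-size statement with the numbers printed in it, and it fails in three ways. The two effect sizes contradict each other. Neither gives 90% power with 27 per group in a plain two-group comparison. And a standardised mean difference sized a trial whose primary test compares two proportions, which generally has less power for the same underlying effect.

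At stake is a stated property of the design. The article implies a 10% chance of missing the planned effect on the primary hypothesis. The actual chance is several times that, and anyone weighing the result needs the true figure.

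**Working it through.** **Inputs.** From Design and Sample Size: d = 0.60, f = 0.35, power 90%, two-sided alpha 0.05, 27 per group evaluable, 10% drop-out, 30 per group recruited. From Statistical Analyses: chi-square or Fisher for CGI-I response, with drop-outs counted as failures. Assumed, because the document gives neither: a control response of 40-70%, and a rule for converting d to responder rates.

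**What reproduces.** 1.56 - 0.97 = 0.59, close to d = 0.60. 54/0.9 = 60.

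**d against f.** For two equal groups f = d/2. So d = 0.60 gives f = 0.30, and f = 0.35 gives d = 0.70.

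**Unadjusted comparison of means.** Non-centrality is d × √(n/2) with 2n - 2 degrees of freedom. For d = 0.60 and n = 27 it is 0.60 × √13.5 = 2.205, and the non-central t gives 58.1% power. As a check, the normal approximation gives Φ(2.205 - 1.960) = 59.7%.

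| Effect | Power, 27 per group | Power, 30 per group | n per group for 90% |
|---|---|---|---|
| d = 0.60 | 58% | 63% | 60 |
| d = 0.70 (f = 0.35) | 71% | 76% | 44 |

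The last column agrees with 2 × (1.960 + 1.282)²/d², which gives 59 and 43 before the small t correction. Working backwards, 90% power is reached at d of about 0.90 with 27 per group and about 0.85 with 30.

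**Baseline-adjusted ANCOVA.** Adjustment raises the effective effect to d/√(1 - r²), where r is the pre-post correlation. With 27 per group this must be about 0.90. For d = 0.60, r = 0.75 gives 0.60/0.661 = 0.907. For d = 0.70, r = 0.63 gives 0.70/0.777 = 0.901. At r = 0.5, power is 70.5% and 83.0%.

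**Planned primary test.** d = 0.60 was converted in two usual ways:
- Probit: p1 = Φ(Φ⁻¹(p0) + 0.60).
- Logit: odds ratio = exp(0.60 × π/√3) = 2.97.

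Power is by exact enumeration of all outcomes, shown as 27 / 30 per group.

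| Control | Experimental | Chi-square | Fisher |
|---|---|---|---|
| 40% | 63.6% (probit) | 38.5 / 45.9% | 28.7 / 35.6% |
| 40% | 66.4% (logit) | 47.3 / 55.1% | 36.8 / 44.5% |
| 50% | 72.6% (probit) | 39.2 / 43.3% | 29.7 / 33.4% |
| 50% | 74.8% (logit) | 46.9 / 51.0% | 36.7 / 40.7% |
| 60% | 80.3% (probit) | 38.9 / 40.5% | 27.3 / 30.9% |
| 60% | 81.7% (logit) | 43.8 / 45.7% | 31.3 / 35.6% |
| 70% | 87.0% (probit) | 35.2 / 35.7% | 20.9 / 25.2% |
| 70% | 87.4% (logit) | 36.9 / 37.5% | 22.2 / 26.7% |

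By the normal approximation, 90% power would need about 73 to 122 per group over these rates.

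**Drop-outs as failures.** If 10% of each arm are counted as failures, both rates are multiplied by 0.9. For example, 50% against 72.6% becomes 45% against 65.3%. With 30 per group and the probit rates, chi-square power falls to 25-39% and Fisher to 18-29%.

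**Detectable effect on the primary.** With 30 per group and 50% control response, before any drop-out dilution, 90% power needs about 88% responders by chi-square or 90% by Fisher.

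**The case against.** The strongest defence is that N = 54 came from a calculation the article does not describe. Quoting f suggests an F test, and an ANCOVA with r of about 0.63 at f = 0.35 would give 90% with 27 per group. Some between-group repeated-measures set-ups also land near 54: at f = 0.35 with three occasions, a correlation of 0.3 gives 48 and 0.5 gives 60. This much stands: a reader might infer a plain arithmetic slip, but the document supports only that the figure cannot be reproduced from what it states. The defence does not rescue the 90%, because no correlation is given and the primary test is neither an ANCOVA nor a repeated-measures test. A one-sided test does not explain the figure either. The text says two-sided, and one-sided power with 27 per group is 70% at d = 0.60 and 81% at d = 0.70.

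The binary figures rest on assumed control rates and an assumed conversion, so they are a range and no single value belongs in the protocol. No combination tried comes near 90%.

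A reader might also infer that the trial will more likely than not miss the effect it was planned for. On the continuous scale, where the effect was stated, power is above one half. On the responder scale it is mostly below one half, but a logit conversion reaches 55% by chi-square with 30 per group before drop-outs are counted.

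Nor does the Discussion concede a small effect for this trial. It reports from a meta-analysis that "additive studies show significant, although small, effects of additive components", then argues that the contrast here may be larger than in conventional dismantling studies.

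Finally, a reader might expect a non-significant result to be reported as showing that behavioral experiments add nothing. The document states no such rule.

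**Conclusion.** The point holds. The 90% power claim does not follow from its stated inputs: it is 58% at d = 0.60 or 71% at f = 0.35 with 27 per group, and 63% or 76% with all 30, for an unadjusted two-sided comparison. These figures, and the contradiction between d and f, need no assumption beyond the printed numbers and the unadjusted test.

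For the primary test as planned, power is about 35-47% (chi-square) or 21-37% (Fisher) with 27 per group, and about 36-55% or 25-45% with 30. This assumes 40-70% control response and a probit or logit conversion of d = 0.60. The drop-out rule lowers it further, so the six added patients do not restore the planned power. Whether an undisclosed method lies behind N = 54 cannot be told from the article.

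**What to change.** Keep N = 60 and correct the statement:

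1. Reconcile d and f: d = 0.60 with f = 0.30, or f = 0.35 with d = 0.70.
2. Settle the primary endpoint. The Abstract names the LSAS; Outcome Measures and Analysis of Outcome Variables name the CGI-I responder rate.
3. Replace the 90% statement with the power of the actual primary test, naming chi-square or Fisher, giving the assumed control and experimental responder rates, and applying the drop-outs-as-failures rule.
4. State the effect detectable with 90% power: d of about 0.85 (30 per group) to 0.90 (27 per group), or about 50% against 88-90% responders with 30 per group before drop-out dilution.
5. Report the responder comparison as a risk difference with a 95% confidence interval. This is good reporting practice at this sample size, not the correction of an error.

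The cost is wording only, with no extra patients or visits. The drawback is that the stated power becomes less favourable.

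### The 10% drop-out allowance (54 to 60) fits an analysis that excludes drop-outs, not the ITT responder test, which keeps all 60 and counts drop-outs as failures

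*Protocol article*

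**What the plan says.** Design and Sample Size (the text after Fig. 1) plans for d = 0.60, also given as f = 0.35. It reports "A power analysis with 90% power on a two-sided test where α = 0.05" leading to 54 patients, 27 per group. It then says, citing previous studies, "we expect a drop-out rate of 10" percent, and concludes "Thus, 60 patients (30 per group) will have to be recruited".

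Statistical Analyses defines the term by attendance: "Patients allocated to treatments will be classified as drop-outs if they miss more than 25% of the sessions". For the responder outcome it adds: "In the ITT analyses of treatment response, drop-outs will be considered as failures". It also says "All statistical analyses will be conducted on the intent-to-treat (ITT) sample and completer sample", without stating which of the two carries the main conclusion.

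The primary outcome is the proportion of CGI-I responders at post-treatment, tested by chi-square or Fisher's exact test. Selection of Patients adds that those who discontinue are asked to complete all assessments.

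**The concern.** An allowance of 1/(1 − drop-out) replaces patients who disappear from the analysis. In the ITT responder test nobody disappears. Patients who drop out remain in the denominator as non-responders in both arms, which pulls both response rates, and the gap between them, towards zero. Extra recruitment restores the headcount but not the gap.

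The six additional patients are presented as protection against drop-out. For the ITT test they may protect only in part, and a reader of a null ITT result would set it against a power that was not worked out for that test.

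**Working it through.** **Inputs from the article.** N = 54 (27 per group), two-sided 0.05, 90% power, d = 0.60, 10% drop-out, target 60. **Assumed here:** 10% drop-out in each arm under the attendance definition, and all response rates, since the article gives none.

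**1. The plan's own step.** 54/0.9 = 60 and 27/0.9 = 30. The arithmetic is exact. For the completer analysis, 60 × 0.9 = 54, the number asked for.

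**2. ITT test, planned effect holding among completers.** Each ITT response rate is 0.9 × the completer rate + 0.1 × 0, so the difference is multiplied by 0.9. Treating this as a factor of 0.9 on the standardised effect, and noting that the test's signal grows with the square root of N:

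- factor = 0.9 × √(60/54) = 0.949
- signal at 90% power = 1.960 + 1.282 = 3.242
- power = Φ(0.949 × 3.242 − 1.960) = Φ(1.115) = 86.8%

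Restoring 90% would take 54/0.81 = 66.7, which is 68 with equal arms.

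**3. ITT test, planned effect already counting drop-outs as failures.** There is no dilution: Φ(√(60/54) × 3.242 − 1.960) = Φ(1.457) = 92.7%. Here 54 would have been enough and no allowance is needed.

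**4. Binary scale, completer effect.** For each assumed control rate, the treated rate is set to give 90% at 27 per arm. Both rates are then multiplied by 0.9 and power is taken at 30 per arm. The formula is power = Φ((difference − 1.960 × pooled SE)/unpooled SE).

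| Control (assumed) | Treated | 27 per arm | 30 per arm, rates × 0.9 |
|---|---|---|---|
| 10% | 48.7% | 90% | 88.4% |
| 20% | 61.7% | 90% | 87.5% |
| 30% | 72.4% | 90% | 86.3% |
| 40% | 81.5% | 90% | 84.6% |
| 50% | 89.1% | 90% | 82.1% |
| 55% | 92.4% | 90% | 80.3% |

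The loss runs from about 2 to 10 points. Exact enumeration gives the same pattern, with losses reaching about 12 points at the 55% control rate. These pairs are chosen to produce 90%. On the logistic scale they correspond to d of about 1.0 to 1.3, well above 0.60.

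**5. At the plan's own d = 0.60.** By t test, power is 58% at 27 per arm, 63% at 30 per arm undiluted, and 54% at 30 per arm with d × 0.9 = 0.54. For a binary example, d = 0.60 gives an odds ratio of exp(0.60 × π/√3) = 2.97. With an assumed control rate of 45%, the treated rate is 71%. Exact chi-square power is 47.1% at 27 per arm, 53.4% at 30 evaluable per arm, and 44.9% at 30 per arm with drop-outs as failures.

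**6. The base figure.** Per arm, 2 × (3.242/0.60)² = 58.4, so 59 (118 in total; 60 per arm by t test). The stated 54 is not reproduced at d = 0.60.

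**The case against.** The strongest reply is that the allowance does fit a planned analysis. The completer analysis is planned alongside ITT, neither is ranked first, and 60 recruited leaves it with 54. That stands. A reader might infer that the sizing contradicts the trial's primary analysis rule, but the article does not designate ITT as that rule. It does not rescue the sentence either, because the sample size section never says its power refers to completers.

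Second, a reader might infer that 60 patients necessarily fall short of the power claimed for 54, whatever the starting number. The article does not support that. The effect size comes from a meta-analysis, and nothing says whether drop-outs are already counted in it. If they are, step 3 applies and power rises. What survives under either reading is that dividing by 0.9 is not the right adjustment for the ITT test.

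Third, the 10% comes from previous studies and may not use the attendance definition, so applying it here is an assumption. Fourth, the larger binary losses need effects far above the planned one; at d = 0.60 the loss relative to 27 evaluable per arm is about 2 points in the binary example and 4 by t test. Fifth, the base N is the bigger problem. The last two points limit the importance of this one, but correcting the base N alone would leave the mismatch in place.

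**Conclusion.** The point holds in a conditional form. The step from 54 to 60 is arithmetically exact and suits the completer analysis, but it does not match the ITT test of the primary CGI-I response.

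If the planned effect is a completer effect and drop-out is about 10% in each arm, a nominal 90% becomes about 87% on the standardised scale, and is about 2 to 10 points lower on the binary scale over assumed control rates of 10% to 55%. If the effect already includes drop-outs as failures, the same 60 patients would give about 93%.

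These figures take the 90% as given only to isolate the effect of the drop-out rule. That 90% is not reproduced at d = 0.60, where 27 per group gives about 58%; this is a separate and larger fault. The present point is modest in size but should be corrected, because the stated power is not tied to an analysis set.

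**What to change.** Keep 60 patients. In Design and Sample Size:

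- Name the analysis set to which the power refers, and remove the implication that 54/0.9 = 60 preserves power for the ITT responder test.
- Restate the power of that chi-square or Fisher test with all 30 per group analysed. Use explicitly assumed response rates that count drop-outs as failures: completer rates multiplied by 0.9, or rates already on that basis used unchanged.
- Show the range over plausible control rates. As an illustration, assumed completer rates of 45% and 71% become about 40.5% and 64%, with power of about 45%.

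The cost is a short new calculation on the responder scale, since the article gives no response rates to rescale, and a few rewritten sentences. The restated power will probably be lower than 90%, mainly because of the base figure. No patients are added, and the drop-out rule and the planned tests stay as they are.
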